**Background/rationale**

Technology is advancing and becoming smarter. The smartphone plays a key role in this advancement, with estimates suggesting that 1.82 billion smartphones were globally in use at the end of 2013 (Khalaf, 2013). Aside from communication, smartphones have numerous other applications or functions that can be accessed via ‘apps’. This variety has promoted a dependency on smartphone use, with estimates suggesting that users check their devices every 6.5 minutes on average (Khalaf, 2013). This increase in use highlights the potential for smartphones to be used as a means to disseminate psychological interventions to the general public, in a cost-effective and widely accessible manner.

Positive psychology models suggest that happier people are more likely to acquire favourable life circumstances, which in turn is likely to engender greater happiness in the long-term (Lyubomirsky et al., 2005). Specifically, investing in ones’ own well-being has been linked to marked benefits across a range of characteristics and resources most valued by society, such as longer life expectancy, higher earnings, and better relationships (Lyubomirksy et al., 2005). For smartphone users looking to increase their happiness, there are now thousands of applications, or ‘apps’, available to them. Smartphone apps may be more accessible, flexible, interactive, and private than other forms of self-help (Howells, Ivtzan, Eiroa-Orosa, 2014). However, despite these potential advantages, few studies have empirically tested whether smartphone apps are an effective means of increasing well-being in the general public (Howells, Ivtzan, Eiroa-Orosa, 2014).

One particular psychological tool that has shown promise as a means of increasing well-being is mindfulness. Mindfulness involves focusing on the present moment, in a non-judgemental, non-reactive way (Kabat-Zinn,1994). The practice has historically been associated with Buddhist teachings dating back several thousand years, and was introduced to the West in the 1970’s (Chiesa & Malinowski, 2011). Since then, a wealth of scientific research has outlined a variety of positive impacts of mindfulness meditation on health and well-being, including reductions in cognitive vulnerability and emotional distress (Shapiro and Carlson, 2009, Baer 2003). Further, multiple studies have linked the practice of mindfulness with increased quality of life and reduced stress (Reibel, Greeson, Brainard, & Rosenzweig, 2001; Shapiro, Schwartz, & Bonner, 1998; Williams, Kolar, Reger, & Pearson, 2001). Mindfulness meditation is also the cornerstone of the well-known Mindfulness Based Stress Reduction Programme (MBSR), originally designed to treat a range of conditions in both clinical and non-clinical populations. MBSR typically takes the form of an 8-week, in-person, group-based programme, coupled with approximately 45 minutes of home practice per day.

Meta-analyses have linked mindfulness training to changes in brain regions associated with attention, memory, self and emotional regulation (Fox et al., 2014). Organisations such a Google and the US army use mindfulness training to improve work place functioning (Jha et al., 2015). The rationale for such interest is based on evidence that mindfulness impacts positively on human functioning (Brown, Ryan & Creswell, 2007). Various mechanistic models have been presented in an attempt to outline how mindlessness-based interventions convey such benefits. Vago and David’s (2012) self-awareness, self-regulation and self-transcendence model (S-ART) provides a theoretical framework based on a neurobiological model describing how mindfulness reduces biases to self-processing and promotes psychological health. Shapiro’s model (2006) outlines the fundamental change in an individual’s relationship to experience (perceiving) following mindfulness training, which leads to changes in self-regulation, and increased cognitive and behaviour flexibility. From a more evolutionary perspective, Williams (2010) suggests mindfulness brings about changes in the way emotions are processed, guiding individuals on how to learn to discriminate between different emotions.

In a recent study, Howells, Ivtzan and Eirosa (2014) examined the impact of a smartphone-based intervention on measures relating to well-being. Their randomised controlled trial examined the impact of 10 days of a Headspace mindfulness intervention using a cohort of ‘happiness seeking’ participants, and measured satisfaction with life, flourishing, positive and negative affect, and symptoms of depression. Relative to a control group, they reported statistically significant increases in positive affect and reductions in depressive symptoms following 10 days of Headspace use, but did not find statistically significance benefits with regards to life satisfaction, flourishing or negative affect scores.

The present study aims to both replicate and extend Howells and colleagues study by investigating the impact of Headspace over a longer (30-day) period, while measuring life satisfaction, stress, and resilience, in a cohort of healthy participants from the general population. The study aims to test whether a smartphone-based mindfulness intervention, delivered via the Headspace app, can lead to significant improvements in psychosocial outcome measures over a longer intervention period.

**Aims/objectives**

This study aims to identify:

- If self-reported measures of stress, life satisfaction, and resilience, improve after 10 and 30 days of a mindfulness-based app (Headspace) intervention, relative to a wait-list control group.

- If there is a linear or non-linear change in scores between baseline, day 10, and day 30 in the experimental condition.

- If those who experience the largest reductions in stress also experience the largest increases in resilience.

**Hypotheses**

H1: The control group will have significantly worse scores on all measures at day 10 and day 30 day compared to the experimental (Headspace) group.

H2: There will be a greater positive impact on study outcomes following 30 days of Headspace use relative to 10 days.

H3: Those who experience larger reductions in stress across 30 days of the Headspace intervention will also experience larger increases in resilience over the same time period.

**Research Methodology**

This study will use a repeated-measures, between-group, randomised controlled design.

Participants will only be selected if they indicate good general health, no prior experience with mindfulness practice, and no recent adverse life events, as assessed via an initial screening tool. Those who meet inclusion criteria and respond within the recommended time period of two weeks will be directed to a webpage, via the Survey Monkey platform, and a detailed participant information sheet. Participants will be informed that they will be randomly assigned either to an experimental group or to a ‘wait-list’ control group, and will be asked to provide informed consent before completing a brief demographics questionnaire. Participants will then be randomly allocated to the Headspace intervention or to a control group. The control group will be informed that they are a ‘wait-list’ group, and will be required to complete questionnaire measures at baseline, and 10 and 30 days later, before being offered access to the Headspace intervention for a further 30 days (should they wish to use it). They will be given detailed instructions of how to download and use the Headspace intervention via their smartphone at the end of the wait-list period. The treatment group will be given instructions to complete questionnaire measures at baseline and then again at 10 and 30 days of the Headspace intervention. Following baseline measures, participants in the Headspace group will be given an access code and details of how to download the Headspace programme to their smartphone. Participants will be gently encouraged to use the app every day during the 30-day study period, and to retain a diary to record hours/days of activity/usage. Between days 9 and 10 of the Headspace intervention, participants in both groups will receive an email encouraging them to complete all outcome measures again via Survey Monkey. Another email reminder will be sent out within 24 hours of completing the full 30-day intervention. If no action is taken further emails will be sent within 5 days of completion. Participants in both groups will be reminded they have the right to withdraw at any point during the study.

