**Recruitment of Participants**

Opportunistic and snowball sampling will be applied via an email asking for volunteers from the general population to take part in a study on mindfulness and well-being (see Appendix for email copy). Those that respond within a two-week time period will be guided to a webpage on Survey Monkey, which will introduce the research and screening procedure. If the participant passes the screening tool, they will be randomly assigned to an experimental group or a control group. The target sample size is 60 participants in total. For those who do not meet inclusion/exclusion criteria, they will be immediately debriefed and further guidance provided.

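### The outcome scales are first completed after allocation, and after controls learn they are wait-listed, so baseline self-reports can be influenced by knowledge of arm

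*Protocol*

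**What the plan says.** The Research Methodology section of the protocol gives the order of events. After screening and the information sheet, participants "will be asked to provide informed consent before completing a brief demographics questionnaire". Next comes allocation, followed at once by disclosure to the controls: "Participants will then be randomly allocated to the Headspace intervention or to a control group. The control group will be informed" of its wait-list status. The baseline scales appear only after allocation, and separately for each arm.

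- Control arm: "The control group will be informed that they are a ‘wait-list’ group, and will be required to complete questionnaire measures at baseline".
- Headspace arm: "The treatment group will be given instructions to complete questionnaire measures at baseline and then again at 10 and 30 days of the Headspace intervention".
- App access: "Following baseline measures, participants in the Headspace group will be given an access code".

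The Recruitment of Participants section gives a shorter account: "If the participant passes the screening tool, they will be randomly assigned to an experimental group or a control group". It mentions no baseline outcome step between screening and assignment.

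The Materials section shows what exists before allocation: the screening items, including the GHQ-28, and age and gender. The three outcome scales are listed separately. The Aims section describes the outcomes as self-reported. The Statistical Analysis section plans a repeated measures ANOVA with group and time as factors, and baseline is one of the three time points.

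**The concern.** A baseline score should be fixed before anything that differs between the arms can act on it. Here, a control participant has been told that the app is postponed before giving the first ratings of stress, life satisfaction and resilience. A Headspace participant has received instructions as a member of the treatment group. Disappointment or anticipation could move the answers in either direction.

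Two things are at stake. First, baseline enters the group-by-time contrast directly, so a baseline difference created by disclosure can look like a differential change over time. The same scores feed the within-group t-tests between time points and the correlation of changes in H3. Second, a participant who leaves between learning the arm and completing baseline has been randomised but has no stress, life-satisfaction or resilience score at any time. With 60 participants in total, and assuming 30 per arm, each such loss is 1/30, or 3.3%, of an arm.

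**Working it through.** **Order of steps.** The protocol gives no figure on this point to reproduce, so the main check is a reading of the sequence.

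| Step | Research Methodology | Recruitment of Participants |
|---|---|---|
| 1 | Screening | Screening |
| 2 | Information sheet and consent | not mentioned |
| 3 | Demographics | not mentioned |
| 4 | Random allocation | Random assignment |
| 5 | Controls told they are wait-listed | not mentioned |
| 6 | Baseline scales, instructed by arm | not mentioned |
| 7 | Access code (Headspace arm) | not mentioned |

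No section places an outcome scale before step 4. Step 7 keeps app use out of the baseline scores. It does not keep out knowledge of the arm.

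**Illustration of the consequence.** The target of 60 comes from Recruitment of Participants. Everything else is assumed:

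- n = 30 per arm (no allocation ratio is stated)
- two-sided 5% test
- no true effect of the app
- SD of 1 at each time
- correlation r of 0.5 to 0.7 between baseline and follow-up
- a disclosure-induced baseline difference of s SD between the arms, of which a fraction p is still present at follow-up.

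The contrast is change from baseline to one follow-up, compared between arms. This is the group-by-time contrast for two time points, not the overall three-level F test.

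- Size of the bias in the change contrast: s × (1 − p)
- SD of a change score: √(2(1 − r))
- Standardised bias: d = s(1 − p) / √(2(1 − r))
- Noncentrality of the t-test on 58 degrees of freedom: d × √(n/2) = d × √15

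Worked case with r = 0.6, s = 0.2, p = 0: d = 0.2/√0.8 = 0.2236. The noncentrality is 0.2236 × 3.873 = 0.866, and the false-positive rate is 13.6%.

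False-positive rate when the shift is gone by follow-up (p = 0):

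| Shift s | r = 0.5 | r = 0.6 | r = 0.7 |
|---|---|---|---|
| 0.1 SD | 6.7% | 7.1% | 7.8% |
| 0.2 SD | 11.9% | 13.6% | 16.6% |
| 0.3 SD | 20.8% | 24.8% | 31.4% |

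A simulation of 20,000 runs agrees: 12.0% and 17.1% for 0.2 SD, and 20.4% and 31.5% for 0.3 SD, at r = 0.5 and 0.7. With no baseline shift it returns 4.9% and 5.1%.

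**Dependence on persistence.** If baseline is moved ahead of allocation, the baseline shift is zero by design, but whatever persists at follow-up, s × p, remains in the comparison. For s = 0.2 and r = 0.6:

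| Fraction persisting | Bias and rate, order as written | Bias and rate, baseline first |
|---|---|---|
| 0 | 0.2 SD, 13.6% | 0, 5% |
| 0.5 | 0.1 SD, 7.1% | 0.1 SD, 7.1% |
| 1 | 0, 5% | 0.2 SD, 13.6% |

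The figures for p = 0 are therefore the worst case for the order as written. In the last row, the bias under the reordered plan is ordinary reporting bias from an unblinded wait-list comparison.

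**The case against.** The strongest case on the other side has five parts.

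- **The text may describe each arm in turn rather than list steps.** The control-arm account does run on to the later offer of the app. But the section uses words of sequence throughout, each arm is instructed on baseline as a group already formed, and nothing places the scales earlier. If another order is intended, the text still needs correction.
- **Disclosure before baseline is explicit for controls only.** This stands. For the Headspace arm it is an inference from arm-specific instructions.
- **The Recruitment section is weak support.** This also stands. It omits consent and demographics too, so its silence about baseline shows little. The point rests on Research Methodology.
- **The error rates depend on a shift that fades.** This stands, and the persistence table shows it. No shift size has a basis in the document.
- **H1 is worded as a comparison at days 10 and 30, which need not use baseline.** True of the wording of H1. The analysis actually planned, however, includes baseline as a time level, and the Aims speak of improvement relative to control.

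A reader might infer more than the protocol supports. It does not show that baseline scores are contaminated, only that the order permits influence. An early leaver would not be without any data: the GHQ-28, age, gender and demographics would exist, and only outcome data would be missing. Nor does anything show that such departures would differ between arms. Participants are told of the possible wait-list before consent, and controls are offered the app afterwards, both of which may limit them. Adjusting for a baseline affected by allocation would be a further problem, but the protocol plans no model with baseline as a covariate.

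**Conclusion.** The point holds as a defect in the order of procedures. As written, the three self-reported outcomes are first measured after allocation and after controls know their arm. Baseline can therefore be influenced by knowledge of allocation, and a participant can be randomised without ever giving an outcome score.

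The bias in the group-by-time contrast is the part of any disclosure-induced baseline difference that does not carry through equally to follow-up. The document gives neither its size nor its direction. The rates of about 7–8%, 12–17% and 21–31% for shifts of 0.1, 0.2 and 0.3 SD are illustrations. They assume 30 per arm, no true effect, correlations of 0.5 to 0.7 and a shift absent at follow-up, and they fall towards 5% as the shift persists.

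This is not a matter for an analysis plan: the protocol itself fixes the order, and no analysis can recover a baseline that was never taken before disclosure.

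**What to change.** In Research Methodology and Recruitment of Participants, state one order: screening, consent, demographics, all baseline outcome scales, then randomisation, then disclosure of arm and, for the Headspace group, the access code. Add that only participants who have submitted the baseline scales are randomised, so that every randomised participant has baseline outcome scores.

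The cost is reordering the survey pages and rewriting a few sentences, with no added assessments. It has to be done before enrolment, because a baseline taken after disclosure cannot be repaired later. The protocol should not present the change as removing reporting bias at days 10 and 30: participants still know their arm, and that limitation of the wait-list comparison remains.

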**Materials**

*Screening Tool*

The initial screening tool has been partly designed by the researchers, though some items have been drawn from existing screening tools, as well as recommendations from Kuyken, Crane and Williams (2012) within their paper on MBCT Implementation. Recent pilot work conducted by City University (Bogosian et al., 2016) investigating an online-based mindfulness intervention for multiple-sclerosis patients recommends the use of the General Health Questionnaire as a screening tool in mindfulness research. Additional screening items will include questions regarding the presence of any serious psychological disorders (such as psychosis and substance abuse, post-traumatic stress disorder, depression), prior or current attendance of a psychological therapy programme, prior formal training or engagement with mindfulness programmes and meditation, the presence of any recent or foreseeable difficult life events (such as a divorce, or moving house), and the presence of any physical illness that is likely to cause acute pain or discomfort. Many of these may impede engagement with the intervention and therefore impair the emergence of any potential benefits associated with it. Participants will also be asked to provide basic sociodemographic information (age and gender).

The General Health Questionnaire 28 (Goldberg, 1978) is a 28-item measure specifically designed as a screening tool and to assess four factors of distress over the previous two weeks – depression, anxiety, social impairment and hypochondriasis. Test-retest reliability has been reported to be high (0.78 to 0.9) (Robinson & Price, 1982) and interrater and intrarater reliability have both been shown to be excellent (Cronbach's α 0.9–0.95) (Failde and Ramos 2000). Responses 1 and 2 (not at all/no more than usual) are assigned a score of zero, whereas a score of 1 is assigned to “rather” responses - more than usual/much more than usual – as per original authour recommendations. Total scores exceeding 4 out of a possible 28 will be excluded from the research as this suggests probable distress.

*Outcome Measures:*

The Satisfaction with Life Scale (1985) is a narrowly focused scale to access global satisfaction. It is shown to have strong psychometric properties including internal consistency and high temporal reliability (Diener, Emmons, Larsen, & Griffin, 1985). It consists of five brief statements and respondents are instructed to give answers using a seven-point Likert Scale.

The Perceived Stress Scale (1983) is a 10-item scale designed to measure the degree to which situations in an individual’s life might be interpreted as stressful. Respondents answer questions about their feelings and thoughts using a 5-point Likert scale (0=never to 5=very often). It has high validity and test-retest reliability (Cohen, Kamarck, Mermelstein, 1983).

The Wagnild Resilience Scale (1993) is a 14-item scale designed to measure five characteristics of resilience. Respondents answer using a 7-point Likert Scale. The scale has good internal consistency, internal reliability, and construct validity (Wagnild, 1993).

An evaluation scale based on Lyubomirsky & Layous, 2013. This measure seeks to assess the number of days of completed activity along with the extent to which participants enjoy the activity and to the extent to which any difficulties are encountered.

**Recruitment of Participants**

Opportunistic and snowball sampling will be applied via an email asking for volunteers from the general population to take part in a study on mindfulness and well-being (see Appendix for email copy). Those that respond within a two-week time period will be guided to a webpage on Survey Monkey, which will introduce the research and screening procedure. If the participant passes the screening tool, they will be randomly assigned to an experimental group or a control group. The target sample size is 60 participants in total. For those who do not meet inclusion/exclusion criteria, they will be immediately debriefed and further guidance provided.

**Statistical Analysis**

Analysis will be carried out using repeated measures analysis of variance (ANOVA) with group (mindfulness vs control) and time as factors (baseline, day 10, day 30). Pearson’s correlational analysis will also be conducted to explore whether potential gains in well-being experienced by the experimental group are related to participants’ subjective ratings of task enjoyment and task difficulty. Post-hoc t-tests will also be conducted to assess mean score differences between the three time points in each group.

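### The planned group-by-time ANOVA uses baseline as an outcome level, so no named test gives the arm differences in H1, and precision is lost that baseline adjustment would recover

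*Protocol*

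**What the plan says.** The Statistical Analysis section of the protocol fixes the method: "Analysis will be carried out using repeated measures analysis of variance (ANOVA) with group (mindfulness vs control) and time as factors". The levels follow in the same sentence: "time as factors (baseline, day 10, day 30". The follow-up tests are described this way: "Post-hoc t-tests will also be conducted to assess mean score differences between the three time points in each group". No baseline-adjusted comparison between arms is named.

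The hypothesis this analysis must serve is H1: "The control group will have significantly worse scores on all measures at day 10 and day 30 day compared to the experimental (Headspace) group". The Research Methodology section describes the design: "This study will use a repeated-measures, between-group, randomised controlled design".

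That section also foresees missed surveys and withdrawal, without giving a rate: "If no action is taken further emails will be sent within 5 days of completion" and "Participants in both groups will be reminded they have the right to withdraw at any point during the study". On size, the Recruitment of Participants section says: "The target sample size is 60 participants in total". It gives no effect size, SD, correlation, power or dropout allowance.

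**The concern.** There are two separate problems.

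**Mismatch with H1.** H1 is about the difference between arms at two follow-up occasions. The interaction F test asks whether the arms' profiles over three occasions differ. It does not estimate the difference at day 10 or at day 30. The post-hoc t-tests do not fill the gap, because they compare occasions inside each arm. A significant change in one arm and a non-significant change in the other is not evidence of a difference between arms.

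**Lost precision.** Because baseline is an outcome level, the interaction uses change from baseline. In a randomised trial the expected baseline difference is zero, so the same baseline data can be used as a covariate, which gives a smaller variance. Classical repeated-measures ANOVA also needs all three occasions, so a participant who skips day 10 but returns at day 30 is lost from both.

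With 60 people, a loss of this kind can decide whether a moderate effect is detected.

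**Working it through.** **Inputs.** The total of 60, the three occasions and the model come from the protocol. Assumed, because the protocol does not give them: 30 per arm, two-sided 5% level, SD 1, true effect d = 0.5 at both follow-ups, and equal correlation ρ between occasions (0.5 to 0.9 shown). The target of 60 has no stated inputs, so there is no planned power figure to reproduce.

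**Step 1: variance for one follow-up day.** With n per arm, the variance of the arm difference is

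- change from baseline: (2/n) × 2(1 − ρ)
- baseline-adjusted: (2/n) × (1 − ρ²)

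The ratio, adjusted to change, is (1 + ρ)/2. So 60 people analysed by change carry the day-30 information of about 60 × 0.75 = 45 analysed with adjustment at ρ = 0.5, 60 × 0.85 = 51 at ρ = 0.7, and 60 × 0.90 = 54 at ρ = 0.8.

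**Step 2: day-30 power, complete data.** Noncentrality is 0.5/√variance, using the noncentral t distribution with 58 df. For example, at ρ = 0.6:

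- change: 0.5/√(2 × 0.80/30) = 2.165, power 57%
- adjusted: 0.5/√(2 × 0.64/30) = 2.421, power 66%

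| ρ | change | adjusted |
|---|---|---|
| 0.5 | 48% | 59% |
| 0.6 | 57% | 66% |
| 0.7 | 69% | 76% |
| 0.8 | 85% | 89% |
| 0.9 | 99% | 99% |

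Allowing for estimation of the baseline slope lowers the adjusted column by about one point or less (58.7% at 0.5, 75.2% at 0.7).

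**Step 3: both days jointly, 2-df test.** This sets the ANOVA interaction beside the joint arm test from a baseline-adjusted mixed model, with the slope correction included. With complete data:

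- ρ = 0.5: 49.3% against 65.5%
- ρ = 0.7: 72.4% against 80.3%
- ρ = 0.8: 88.8% against 91.7%
- ρ = 0.9: 99.6% for both

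Simulation with 3,000 runs per setting agreed at the two correlations simulated (49.0% against 65.8% at ρ = 0.5; 70.9% against 79.6% at ρ = 0.7). Type I error was between 4.4% and 5.4% for both methods across the settings run.

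**Step 4: missed surveys.** Take ρ = 0.6 and 15% missing at each follow-up.

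- *Independent misses.* Complete on all occasions: 60 × 0.85² = 43.4, or 21.7 per arm. With day-30 data: 60 × 0.85 = 51, or 25.5 per arm. Complete-case change: 0.5/√(2 × 0.80/21.675) = 1.840, power 44%. Adjusted, all with day-30 data: 0.5/√(2 × 0.64/25.5) = 2.232, power 59%. Adjusted on complete cases only: 52%. Adjustment and retention therefore each account for roughly half of the gain.
- *The same people miss both.* 51 remain under either method. Change: 0.5/√(2 × 0.80/25.5) = 1.996, power 50%. Adjusted: 59%. Here the whole gain comes from adjustment.

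**The case against.** The strongest reply is that the planned interaction is a legitimate test of differential change, so this is only a preference about efficiency. The first half stands: with complete data the interaction is valid, and its simulated type I error is nominal. A reader might infer that the planned analysis is invalid; the protocol does not support that. But the protocol positively fixes this model and names only within-arm follow-up tests, so the mismatch with H1 is in the stated text and is not detail left to an analysis plan.

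Four further points stand in whole or part.

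- **The gain may be small.** The Materials section describes high temporal or test-retest reliability for the life-satisfaction and stress scales. If correlations over 30 days are near 0.9, the gain vanishes.
- **Exclusion is inferred.** The protocol does not say that incomplete participants are dropped. That follows from the classical form of the method, and the statistical analysis plan, which is not at hand, may handle it. The retention gain also depends on the pattern of misses, as Step 4 shows.
- **Baseline timing is unclear.** The Research Methodology section describes allocation, and telling controls that they are on a wait-list, before it mentions baseline questionnaires. If baseline is answered after allocation is known, it is no longer a clean covariate.
- **Baseline is needed as an occasion elsewhere.** The Aims ask whether change from baseline through day 10 to day 30 is linear in the experimental arm. A model with only follow-up scores as responses cannot answer that directly.

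Three stronger readings should be left aside. Unequal spacing of days 0, 10 and 30 does not by itself show that sphericity fails, and routine corrections exist. The ANOVA group main effect is diluted by baseline, but it is not the natural treatment test here, so its low power is not a fair comparator. And differential disengagement could bias a complete-case comparison, but the protocol gives no rates by arm, and a model that assumes missing at random would not remove bias from informative dropout.

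**Conclusion.** The point holds as a mismatch with H1 and a loss of efficiency. No named test delivers the day-10 and day-30 arm differences that H1 asserts. Compared like for like at day 30 with complete data, baseline adjustment adds about 12 points of power at ρ = 0.5, 10 at 0.6, 7 at 0.7, 3 at 0.8 and essentially none at 0.9. With 15% missing each survey at ρ = 0.6, the gain is between 9 points (same people miss both) and 15 points (independent misses). All of these figures rest on 30 per arm, a 0.5 SD effect and equal correlations, none of which the protocol states. The direction is firmer than the size: the adjusted analysis was never less powerful in the settings examined.

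**What to change.** For H1, name a linear mixed model for each outcome:

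- responses: day-10 and day-30 scores;
- fixed effects: arm, day, arm-by-day, baseline score and baseline-by-day;
- unstructured covariance;
- all randomised participants with at least one follow-up, analysed as randomised.

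Report the arm differences at day 10 and day 30 from this model, with confidence intervals, as the tests of H1.

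Keep a separate analysis within the Headspace arm over baseline, day 10 and day 30 for the linear or non-linear aim. State in Research Methodology that baseline questionnaires are completed before allocation is disclosed.

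The cost is revised analysis wording, a clarified order of procedures and about one degree of freedom; no extra participants or measurements are needed. The model relies on missing at random and still leaves out people with no follow-up, so informative dropout remains a limitation to report.
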